### Exclusion criteria

(1) Valvular atrial fibrillation heart disease;

(2) NYHA cardiac function grade Ⅳ or LVEF<40%, LA diameter >50mm;

(3) Moderate to severe left ventricular hypertrophy (wall thickness >1.5cm);

(4) Patients with acute coronary syndrome or patients requiring stent implantation;

(5) Patients with a history of cardiac surgery and catheter ablation in the past 6 months;

(6) History of atrial fibrillation≥5 years;

(7) Hyperthyroidism;

(8) Patients with atrial fibrillation with cardiomyopathy;

(9) Patients with chronic arrhythmia requiring pacemaker installation;

(10) Patients with known bleeding constitution and left atrial/left auricular thrombus or severe hemostasis and coagulation dysfunction;

(11) Severe hepatic and renal insufficiency [ALT≥3 ULN or eGFR<50ml/min/1.7m^2^];

(12) Patients with neuropsychiatric diseases;

(13) Allergic to the ingredients of the study;

(14) Pregnant or lactating women;

(15) Patients who are participating in other clinical studies;

(16) Patients who are deemed unfit by the investigator to participate in this study.

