## Treatment

**Teat Group:** conventional treatment+ Shensong Yangxin capsule 4 capsules/times, 3 times/day, orally.

**Control Group:** conventional treatment + Shensong Yangxin capsule placebo 4 capsules/times, 3 times/day, orally.

All the above treatments were performed after radiofrequency ablation, and the course of treatment was 1 year

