### Secondary efficacy endpoints

(1) Changes in atrial fibrillation load at 3 months, 6 months, and 1 year after treatment. Atrial fibrillation load was defined as the longest duration of atrial fibrillation episodes, the number of episodes of atrial fibrillation, and the percentage of time patients were in atrial fibrillation during a given monitoring period.

(2) Time of first occurrence of atrial flutter/atrial fibrillation.

(3) Incidence of electrical cardioversion within 1 year after treatment.

(4) Changes of transthoracic echocardiographic indexes at 1 year after treatment.

(5) Incidence of stroke and thromboembolism at 6 months and 1 year after treatment.

(6) Health Survey Summary Form (SF-36) score within 1 year after treatment.

Safety endpoints

(1) Adverse events (AEs): Any adverse medical events occurring between the time subjects signed the informed consent and were enrolled in the study and the last follow -up, regardless of whether there was a causal relationship with the study drug, was considered an adverse event. The sum of "definitely relevant", "possibly relevant" and "unascertainable" associated with the study drug was the adverse reactions (ADRs) of the study drug, and the incidence of adverse reaction was calculated accordingly.

(2) Laboratory indicators: blood routine, urine routine, stool routine, biochemical examination and coagulation function examination;

(3) Clinical physical examination and vitals.

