**Table 1: Summary Form of Health Status Survey (SF-36) scoring criteria**

| **8 dimensions + overall** | **Items** | **Scoring methods for each dimension** |
| --- | --- | --- |
| 1. Physiological Function(PF) | 3.1-3.10 | PF=[(actual score - 10) /20] x 100 |
| 2. Physiological Function(RP) | 4.1-4.4 | RP=[(actual score -4) /4] x 100 |
| 3. Body pain (BP) | 7,8 | BP=[(actual score -2) /9] x 100 |
| 4. Overall Health (GH) | 1, 11.1- 11.4 | GH=[(actual score -5) /20] x 100 |
| 5 Vitality (VT) | 9.1, 9.5, 9.7, 9.9 | VT=[(actual score -4) /20] x 100 |
| 6. Social Function (SF) | 6,10 | SF=[(actual score -2) /9] x 100 |
| 7. Emotional Function(RE) | 5.1-5.3 | RE=[(actual score -3) /3] x 100 |
| 8. Mental Health(MH) | 9.2, 9.3, 9.4, 9.6, 9.8 | MH=[(actual score -5) /25] x 100 |
| Overall: Health Change(HT) | 2 | HT=[(actual score - 1) /4] x 100 |

* Total Body Health measures (PCS) include: PF, RP, BP, GH;

* Total Measure of mental Health (MCS) includes: VT, SF, RE, MH.

* Scoring method for each dimension = (actual score - lowest score)/(highest score - lowest score)×100

* Actual score (for each dimension) = Add the scores for each item

Analysis of safety

Safety evaluation is analyzed on SS populations.

Proportion of antiarrhythmic drugs using within 90 days after radiofrequency ablation will be described in each group using frequencies and percentages. The range of antiarrhythmic drugs within 90 days after radiofrequency ablation was defined as the start date of ATC3 drugs between the day of radiofrequency ablation and the 90^th^ day of surgery.

Proportion of adverse events, severe adverse events, adverse reactions, and severe adverse events will be described in each group using frequencies and percentages. If necessary, changes of the laboratory and electrocardiogram variables will be analyzed before and after treatment.

Additional analysis

Additional analyses will be performed to compare primary and secondary endpoints between randomization groups after excluding patients who were still using antiarrhythmic drugs after 90days after radiofrequency ablation. Analysis methods for primary and secondary endpoints analysis described previously will be performed.

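### Adverse events are counted from consent and tabulated by group with no onset limit, so events before the first capsule enter the all-cause proportions and can count as adverse reactions

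*SAP*

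**What the plan says.** Section 3.2 (Safety endpoints) sets the window: "Any adverse medical events occurring between the time subjects signed the informed consent and were enrolled in the study" and the last follow-up. Causality plays no part in the definition: such an event, "regardless of whether there was a causal relationship with the study drug, was considered an adverse event".

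The same item defines a second, drug-attributed measure: "The sum of 'definitely relevant', 'possibly relevant' and 'unascertainable' associated with the study drug was the adverse reactions (ADRs) of the study drug". It filters by relatedness and sets no condition on onset date.

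Section 2.7 (Treatment) places the study drug after the procedure: "All the above treatments were performed after radiofrequency ablation, and the course of treatment was 1 year".

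Section 4 (Selection of populations) defines the safety set as patients who received at least one treatment after randomization. It also removes patients followed for less than 3 months from all analyses. Both rules select patients; neither selects events by onset.

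Section 6.5 (Analysis of safety) gives the output: "Proportion of adverse events, severe adverse events, adverse reactions, and severe adverse events will be described in each group", as frequencies and percentages. It has no treatment-emergent definition and no split into before and after the first dose.

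**The concern.** An event that starts before the first capsule cannot be caused by the capsule. Under these rules it is still counted in its arm's adverse event proportion, provided the patient is later dosed. Adding the same background to both arms makes them look more alike, and in a safety table that makes a real difference harder to see.

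The adverse reaction count has a sharper problem of definition. Unascertainable relatedness is enough for an event to be counted as a reaction, so a pre-dose event rated that way would be reported as a reaction to a drug the patient had not yet taken.

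Elsewhere Section 6.5 does fix dates: it limits antiarrhythmic drug use to start dates from the day of ablation to day 90. The adverse event tables have no comparable rule.

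**Working it through.** **Which events fall in the window.** The sections give this sequence:

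- The window opens at consent and enrolment (Section 3.2).
- The first capsule comes after the ablation (Section 2.7).
- The safety tables set no lower limit on onset (Section 6.5), and the safety set does not supply one (Section 4).

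So every event between consent/enrolment and the first capsule, in a patient later dosed and analysed, is counted.

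**Whether the ablation itself lies in the window.** The SAP does not state the order.

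- Exclusion criterion 5 (Section 2.4.2) bars "Patients with a history of cardiac surgery and catheter ablation in the past 6 months". Read literally, screening after the index ablation would exclude every patient, which suggests that screening comes first.
- Inclusion criterion 4 (first ablation) and the Section 4 restriction to patients undergoing ablation fit either order.
- Section 2.6 places randomization after the baseline assessment, without relating either to the ablation.

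Consent before ablation is therefore likely but not established. If consent follows the ablation, the procedure falls outside the window, but events between consent and first capsule are still counted.

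**Size of the attenuation.** The SAP gives no adverse event rate, so there is no plan figure to reproduce and every rate below is an assumption. Let q be the share of patients in each arm with a pre-dose event, and p the on-drug proportion, independent of the pre-dose events.

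- Tabulated proportion = 1 − (1 − q)(1 − p) = q + (1 − q)p.
- Tabulated risk difference = (1 − q)(p_test − p_control), so it shrinks by the factor (1 − q).

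With assumed on-drug rates of 15% (test) and 10% (control):

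| q | Test | Control | Risk difference (points) | Risk ratio |
|---|---|---|---|---|
| 0% | 15.0% | 10.0% | 5.0 | 1.50 |
| 2% | 0.02 + 0.98 × 0.15 = 16.7% | 0.02 + 0.98 × 0.10 = 11.8% | 4.9 | 1.42 (1.415) |
| 5% | 0.05 + 0.95 × 0.15 = 19.25% | 0.05 + 0.95 × 0.10 = 14.5% | 4.75 | 1.33 |
| 10% | 0.10 + 0.90 × 0.15 = 23.5% | 0.10 + 0.90 × 0.10 = 19.0% | 4.5 | 1.24 |
| 20% | 0.20 + 0.80 × 0.15 = 32.0% | 0.20 + 0.80 × 0.10 = 28.0% | 4.0 | 1.14 |

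Higher assumed on-drug rates give the same pattern. For 28% vs 20%, the ratio of 1.40 becomes 1.36, 1.32, 1.26 and 1.18 at q = 2%, 5%, 10% and 20%. For 50% vs 40%, the ratio of 1.25 becomes 1.24, 1.22, 1.20 and 1.15. Restricting the tables to events from the first dose restores the q = 0 row.

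**Adverse reactions.** By the same formula, if a share r of patients has a pre-dose event rated unascertainable, a true reaction incidence a is reported as r + (1 − r)a in each arm. The SAP gives nothing from which to estimate r.

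**The case against.** Collecting adverse events from consent is not an error, and nothing here says it is; the gap lies only in how the events are tabulated. Four further objections have force.

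- **The order of consent and ablation is not stated.** A reader might infer that procedural complications certainly enter the count. The documents support only that they probably do. The window also refers to enrolment as well as consent, and the interval from ablation to first capsule is not given. This objection stands, though any event before the first capsule is counted either way.
- **The tabulated figure is all-cause.** It is not the drug's own incidence. The drug-attributed measure is the adverse reaction count, and clearly procedural events drop out of it through the relatedness rating. This stands, except for events rated unascertainable, and nothing suggests these would be common.
- **No between-arm safety test is planned.** A reader might infer that the safety comparison loses power. Section 6.5 plans description only and states no hypothesis or power target. The general chi-square or Fisher rule in Section 6.1 could be read across, but Section 6.5 does not invoke it. A power loss should not be claimed.
- **The arms should balance.** In a randomized, double-blind trial, events before any capsule is taken are expected equally in both arms. A reader might infer that the plan favours the test drug or conceals a harm. The documents do not show that; the expected effect is attenuation and noise.

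Risk ratios also make the effect look larger than risk differences do. At q = 10% the difference moves only from 5.0 to 4.5 points.

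**Conclusion.** The point holds as a minor one. Followed as written, the SAP puts pre-dose events into the by-group all-cause proportions and lets a pre-dose event rated unascertainable count as an adverse reaction. This follows from the stated rules and does not depend on the order of consent and ablation, which affects only how many such events there are.

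The comparison is attenuated by the factor (1 − q) on the risk difference. On the assumed 15% vs 10%, the risk ratio falls from 1.50 to between about 1.42 (q = 2%) and 1.14 (q = 20%); if q is near zero, the effect is negligible. This rests on assumed rates, equal q in both arms, and independence of pre-dose and on-drug events. Without independence, the factor (1 − q) applies to the on-drug difference among patients who had no pre-dose event. The size for this trial cannot be established from the SAP.

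**What to change.** Keep collecting adverse events from consent. In Section 6.5:

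- Base the by-group tables of adverse events, severe adverse events and adverse reactions on events that start, or worsen, on or after the first dose of study drug.
- List events between consent and first dose separately, by group.
- State that an event with onset before the first dose, and no later worsening, cannot be counted as an adverse reaction, whatever its relatedness rating.
- Add a rule for partial onset dates. Section 5 replaces a missing start day with the first of the month. If applied to adverse events, that could move an on-drug event to before the first dose in the month when dosing began.

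The cost is SAP wording and one derived flag from adverse event onset and first-dose dates. No new data are needed, provided both dates are recorded, as they normally would be.

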# Selection of populations

All analyses were performed on patients undergoing radiofrequency ablation and will not include patients who were followed for less than 3 months and did not complete the blanking period.

The primary analysis will be for a modified intent to treat population set (mITT), which included all randomized patient with the exclusion of patients that did not provided consent, failure to receive treatment or without any valid data collected after randomization. Following the intention-to-treat principle, patients will be analysed according to the procedure assigned.

Per-Protocol set (PPS) population: a subset of the mITT analysis set, including all patients randomized, treated without major protocol violations/deviation.

pre-defined major protocol violations/deviations are:

- poor compliance in treatment, that is, less than 80% adherence to taking the drug;
- missing data for the primary efficacy endpoint
- major violation of the research protocol, such as non-respect of the randomized procedure allocation and/or duration (wrong procedure followed, premature discontinuation of procedure)

Not pre-defined major protocol deviations identified during a blinded data review before final database lock will be classified.

Safety set (SS): All patients who received at least one treatment after randomization. Patients will be analysed according to procedure received

Measures of efficacy were analysed using mITT and PPS populations, respectively. Safety was analysed by SS population.

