Aimed at changes in atrial fibrillation load at 3 months, 6 months and 1 year after treatment, the mean, standard deviation, median, minimum, maximum, lower quartile (Q1) and upper quartile (Q3) of atrial fibrillation load at each visit site were calculated according to the form of quantitative endpoints. T-test or Wilcoxon rank sum test were used to compare it between the two groups. At the same time, the changes of atrial fibrillation load compared with baseline at 3 months, 6 months and 1 year after treatment were statistically described, and T-test or Wilcoxon rank sum test was used to compare the changes between the two groups.

The time of the first occurrence of atrial fibrillation/atrial fibrillation was analysed as the secondary endpoint. The occurrence days of atrial fibrillation/atrial fibrillation were calculated by the date of radiofrequency ablation surgery as the starting date, the occurrence days= the date of the first occurrence of atrial fibrillation/atrial fibrillation-the date of radiofrequency ablation surgery +1. For patients with atrial flutter/atrial fibrillation, the mean, standard deviation, median, minimum, maximum, lower quartile (Q1) and upper quartile (Q3) of occurrence time were calculated according to the form of quantitative variables. T-test or Wilcoxon rank sum test were used to compare the occurrence time between the two groups.

The secondary efficacy endpoint of transthoracic echocardiography one year after treatment were analysed. The indexes of transthoracic echocardiography mainly included left ventricular end-diastolic volume, left ventricular end-systolic volume, ejection fraction, stroke volume, cardiac output and other evaluation indexes. The mean, standard deviation, median, minimum, maximum, lower quartile (Q1) and upper quartile (Q3) of the results of the evaluation indicators were calculated according to the form of quantitative variables, and T-test or Wilcoxon rank sum test were used to compare the evaluation variables between the two groups.

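### The 3-month follow-up exclusion in SAP section 4 covers all analyses and so contradicts the safety set, the mITT definition and the adverse event window; it should be limited to the primary recurrence analyses

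*SAP*

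**What the plan says.** Section 4 (Selection of populations) begins with a general restriction: "All analyses were performed on patients undergoing radiofrequency ablation and will not include patients who were followed for less than 3 months". The sentence ends by adding that these patients had not completed the blanking period. No analysis is exempted.

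The set definitions that follow impose no minimum follow-up:

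- **Safety set:** "Safety set (SS): All patients who received at least one treatment after randomization".
- **mITT:** all randomised patients, with the "exclusion of patients that did not provided consent, failure to receive treatment or without any valid data collected after randomization".
- **Use of the sets:** "Measures of efficacy were analysed using mITT and PPS populations, respectively. Safety was analysed by SS population".

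Other sections bear on the first 90 days:

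- Section 2.7: study treatment follows ablation and lasts 1 year, so the blanking period is time on study drug.
- Section 3.2: adverse events are those "occurring between the time subjects signed the informed consent and were enrolled in the study and the last follow -up".
- Section 3.1.2: cardioversion is counted within 1 year after treatment, and stroke/thromboembolism at 6 months and 1 year after treatment.
- Section 6.4: days to first AF/flutter "were calculated by the date of radiofrequency ablation surgery as the starting date". Only the primary endpoint is timed from ablation plus 90 days.
- Section 5: patients who do not complete 1-year follow-up stay in mITT and PPS for the primary endpoint, censored at last follow-up.
- Section 6.2: dropouts are listed, with dropout rate and termination reasons.

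**The concern.** Two programmers could follow this SAP faithfully and produce different adverse event tables. One would apply the opening sentence and remove every treated patient who died, withdrew or was lost before 3 months. The other would apply the safety set definition and keep them. Both the denominators and the event counts would differ.

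The first reading matters most for safety. Early withdrawal for intolerance, and early serious events, are what a safety analysis should show, and these patients would be the ones left out. For efficacy events counted from ablation or from the start of treatment, the comparison would be conditioned on staying in follow-up for 3 months. Study drug can affect that, so the remaining groups are no longer fully protected by randomisation.

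**Working it through.** **1. Where a day-90 restriction is needed.** Primary time is the date of recurrence or last follow-up, minus (ablation date + 90), plus 1. A patient last seen 60 days after ablation gets 60 − 90 + 1 = −29 days; one last seen at day 89 gets 0. Such patients cannot contribute time at risk, so leaving them out of this analysis is coherent.

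**2. Where it is not.**

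| Analysis | Clock or window | Are the first 90 days included? | Effect of the opening rule |
| --- | --- | --- | --- |
| Primary recurrence | Ablation + 90 days | No | Appropriate |
| Adverse events | From consent/enrolment | Yes | Early events in early dropouts lost |
| First AF/flutter | Ablation date | Yes | Early dropouts with a recorded event lost |
| Cardioversion | Within 1 year after treatment | Yes | Early events and denominator lost |
| Stroke/thromboembolism | 6 months and 1 year after treatment | Yes | Early events and denominator lost |
| AF load, echocardiography | 3 months or later | Mostly not applicable | Little; data mostly absent anyway |

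For example, a patient with a stroke at day 20 who withdraws at day 30 counts under the safety set and mITT definitions, but not under the opening sentence. The condition about completing the blanking period does not rescue the rule: blanking is itself 3 months (90 days), so it adds practically nothing.

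**3. The plan's own figures.** With 39.8% versus 30%, two-sided 5%, 80% power and unpooled variance:

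n = (1.960 + 0.842)² × (0.398 × 0.602 + 0.30 × 0.70) / 0.098² ≈ 367.4, rounded up to 368 per group.

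Allowing for 20% loss, 368 / 0.80 = 460 per group, 920 in total. Section 2.5 reproduces, so 20% and 920 are usable inputs.

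**4. Illustrative size of the removal.** The SAP gives 20% loss but no timing. Assume a constant rate over 365 days:

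- c = −ln(0.80)/365; share lost by day 90 = 1 − exp(−90c) = 0.0535; × 920 ≈ 49 patients.
- With 10% or 30% loss over the year (assumed, not in the SAP): about 24 or 77.

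Alternatively, fix the loss at 0.20 × 920 = 184 and vary the share that falls before 3 months: 25% gives 46 patients (5% of 920), 50% gives 92 (10%), and 100% gives 184 (20%).

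**5. Illustrative effect on an adverse event rate.** All rates here are assumed: 5% in retained patients, 20% to 50% in early dropouts.

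- 92 early dropouts: (0.20 × 92 + 0.05 × 828)/920 = 6.5%; (0.50 × 92 + 0.05 × 828)/920 = 9.5%.
- 46 early dropouts: (0.20 × 46 + 0.05 × 874)/920 = 5.75%; (0.50 × 46 + 0.05 × 874)/920 = 7.25%.

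In each case the opening rule would report 5.0%.

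**The case against.** The best defence is that the opening sentence is a clumsy statement of the day-90 landmark and that the specific set definitions govern. Sections 4 and 6.5 assign safety analyses to the safety set, whose definition keeps every treated patient. The mITT definition keeps early dropouts who have any valid data after randomisation. On that reading nobody is wrongly removed.

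This defence limits the point but does not dispose of it. A reader might infer that the plan definitely erases early dropouts from its safety results. The document does not support that, because the set definitions read alone would retain them. What it shows is a conflict, and nothing in the SAP says which statement prevails.

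Three further limits stand:

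- Early dropouts do not vanish from all reporting. Section 6.2 lists them with termination reasons. A disposition listing is, however, no substitute for adverse event incidence by arm.
- Not every secondary endpoint is affected. AF load and echocardiography would mostly lack data from these patients anyway. Time to first AF/flutter is summarised only among patients with an event, so only early dropouts with a recorded event matter.
- Simply restoring early dropouts to the cardioversion and stroke proportions is not enough. Section 6.4 compares plain proportions and section 5 does no imputation, so a patient lost at day 30 without an event would in effect be counted as event-free at 1 year.

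**Conclusion.** The point holds as an internal contradiction that must be resolved before analysis. The opening rule of section 4 is wrong as written for safety and for events counted from ablation or treatment start; it is right only for the primary recurrence analyses. The primary result is not challenged.

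The size depends on the reading adopted and on when patients leave. About 49 of 920 is an illustration under constant loss, not a forecast, and the adverse event rates used above are hypothetical. None of these figures shows a difference between arms. That the exclusion may differ by arm is a possibility created by conditioning on post-randomisation follow-up, and the SAP gives nothing from which to estimate it.

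**What to change.** Replace the opening sentence of section 4 with wording such as:

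*The primary recurrence analyses, which start 90 days after ablation, include only patients still in follow-up at that time. This restriction applies to no other analysis.*

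Then state that:

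1. The safety set as defined is used for all safety analyses, with adverse events counted over the window in section 3.2.
2. The mITT set as defined is used for first AF/flutter, cardioversion and stroke/thromboembolism.
3. Cardioversion and stroke/thromboembolism are estimated by Kaplan-Meier or cumulative incidence, with censoring at last follow-up, so that early dropouts without an event are not treated as event-free at 1 year. The between-group comparison should match the estimate chosen.
4. The number lost before day 90 is reported by arm with reasons. This extends the listing already planned in section 6.2.

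The cost is SAP wording, one population flag and modest programming for item 3. No new data are needed, provided the dates of cardioversion, stroke/thromboembolism and last follow-up are recorded.

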# Statistical analysis Methods

General principles of statistical analysis

Statisticians are responsible for developing a statistical analysis plan (SAP) with the principal investigator after the protocol is confirmed. Statistical analysis will be performed with SAS 9.4 (or higher version; SAS Institute, Cary, NC). The sample size is calculated using PASS13 software (NCSS, Kaysville, UT).

A 2-tailed P<0.05 will be considered statistically significant in all statistical tests. (If no other specification). No adjustments for multiple comparisons were made.

Qualitative data will be described with frequencies and percentages; quantitative data will be described with mean and standard error or with median and interquartile interval, minimum and maximum.

Continuous variables will be summarized with mean and SD and compared using paired t-test or Wilcoxon rank test, as appropriate. Categorical variables will be summarized with frequencies and percentages and compared using chi-square test or Fisher exact test, as appropriate. Ranked variables will be compared using Wilcoxon rank test or CMH test.

Enrolment Analysis

Enrollment analysis will summarize the number of enrollment and the number of subjects who completed the trial of each site and lists dropout subjects.

The dataset size between groups, subjects' disposition between sites, dropout rate and termination reasons will be listed in detail

Baseline and demographic characteristics

Baseline characteristics of patients will be described overall and per group.

Demographic and baseline characteristics (age, gender, height, BMI, vital signs, etc.), medical history, family history of atrial fibrillation, drug allergy, etc. of the subjects will be summarized. T-test or Wilcoxon rank-sum test will be used in baseline comparison of continuous variables such as age, height, and BMI between the two groups. The chi-square test or Fisher’s exact test will be used in the baseline comparison of categorical variables such as gender, and medical history

Analysis of efficacy

Both mITT and PPS were used for effectiveness analysis. Analysis performed on PP populations using the same methods can be considered as a sensitivity analysis.

(1) Baseline: The baseline of each relevant efficacy endpoints was described. For comparison methods between groups, refer to the general statistical method above.

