(2) Primary efficacy endpoint: The recurrence rate of atrial fibrillation after ablation was statistically described in the two groups respectively.

Survival analysis was used to statistically analyse the recurrence rate of atrial fibrillation after ablation in the two groups. Kaplan-Meier curve of recurrence of atrial fibrillation after ablation was drawn between the two groups, and Log-rank test was used to compare the endpoint between the two groups. Besides, Cox proportional hazard regression model was used to calculate the risk ratio (HR) and 95% confidence interval (CI) of atrial fibrillation recurrence after ablation in the experimental group and the control group to estimate the efficacy, while considering each site as random effect included in the model.

- If atrial fibrillation recurred within 1 year, it was defined as the occurrence of end event. Time to recurrence of atrial fibrillation within 1 year=date of recurrence of atrial fibrillation-(date of radiofrequency ablation+90 days) +1, calculated by day.
- If the visit specified in the protocol was not completed within 1 year, the follow-up could not be completed by the end of 1 year due to loss of follow-up or withdrawal or other reasons, it was defined as censor, censor time=date of last follow-up-(date of radiofrequency ablation +90 days) +1, calculated in days.
- If the visit was completed within 1 year and no recurrence of atrial fibrillation occurred, it was defined as censor, and the censor time in analysis (1) was the date of last visit- (date of radiofrequency ablation+90 days) +1; The censor time in analysis (2) was 365 days.
- If the visits required by the protocol were completed within 1 year and AF recurred after 1 year, the endpoint was defined as event in analysis (1) and the recurrence time was the date of AF recurrence -(date of radiofrequency ablation+90 days) +1; the endpoint was defined as censor in analysis (2) and the censor time was the last visit- (date of radiofrequency ablation+90 days) +1.

(3) Secondary efficacy endpoints

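### The per-protocol rules on adherence and early stopping have no cut-off at first recurrence, so a valid primary event can be dropped for what the patient did afterwards

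*SAP*

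**What the plan says.** Under Selection of populations, the SAP defines the PPS as "a subset of the mITT analysis set, including all patients randomized, treated without major protocol violations/deviation". Two of the pre-defined major deviations matter here. One is "poor compliance in treatment, that is, less than 80% adherence to taking the drug". The other is failure to respect the randomised allocation or its duration, illustrated by "wrong procedure followed, premature discontinuation of procedure". Neither has a time window, and no denominator is given for adherence.

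Under Treatment, "the course of treatment was 1 year". The primary endpoint is the first recurrence after the 90-day blanking period, analysed as time to event: "If atrial fibrillation recurred within 1 year, it was defined as the occurrence of end event".

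The PPS is used for efficacy: "Measures of efficacy were analysed using mITT and PPS populations, respectively". Its role is given under Analysis of efficacy: "Analysis performed on PP populations using the same methods can be considered as a sensitivity analysis". The mITT set is primary.

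Processing of missing data adds that patients who drop out before 1 year stay in both the mITT set and the PPS, censored at their last follow-up.

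**The concern.** Only drug taken before the first recurrence can influence that recurrence. A patient who takes every dose, recurs at month 5 and then stops has supplied a complete primary endpoint under full exposure. As worded, the adherence and duration rules can still class that patient as a major deviator, and the event leaves the PPS with the patient.

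This selects patients on behaviour after the outcome. If recurrence itself prompts some patients to stop, events are removed more readily than event-free follow-up. If that happens more in one arm, the PPS comparison is biased, and agreement or disagreement with the mITT result becomes hard to interpret.

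**Working it through.** **1. The plan's own figure.** Inputs from Sample Size and the general statistical principles: 39.8% against 30%, two-sided 5%, 80% power, 1:1. With unpooled variance:

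n = (1.960 + 0.842)² × (0.398×0.602 + 0.30×0.70) / 0.098² = 368 per group.

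This reproduces the SAP. The pooled formula gives 371. Allowing for 20% loss, 368/0.80 = 460, also as stated. The design rates imply a hazard ratio of ln(0.70)/ln(0.602) = 0.703. In 368 patients per group they imply about 146 control and 110 treated events. These rates serve below only to scale an illustration.

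**2. Which patients the rules reach.**
- *Adherence rule.* Assume a 365-day denominator (the SAP gives none), full adherence up to recurrence and none after. Adherence is below 80% if drug stops before day 0.80 × 365 = 292. That is (292 − 90)/275 = 73% of the window from day 90 to day 365. With a constant hazard, λ = −ln(1−p)/275, and the share of 1-year recurrences before day 292 is (1 − e^(−202λ))/p. This is 78% at p = 0.398 and 77% at p = 0.30.
- *Duration rule.* If the word procedure means study drug, stopping at any time before the end of the 1-year course is caught.
- *Rescue.* The blinded data review classifies only deviations that were not pre-defined, and these two were. No other section restores such a patient.

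**3. Effect on the PPS.** Let f be the share of recurrent patients removed for what they did after the event (an assumption), with no event-free patient removed. The PPS rate is p(1−f)/(1−pf), and HR = ln(1−rate on drug)/ln(1−rate on control). The last column is the chance of P<0.05 from a two-proportion approximation.

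| True rates (control, drug) | f control | f drug | Events lost (control, drug) | PPS rates | HR | Chance of P<0.05 |
|---|---|---|---|---|---|---|
| 39.8%, 30% | 0 | 0 | 0, 0 | 39.8%, 30.0% | 0.703 | 79.8% |
| 39.8%, 30% | 20% | 20% | 29, 22 | 34.6%, 25.5% | 0.694 | 73.5% |
| 39.8%, 30% | 30% | 30% | 44, 33 | 31.6%, 23.1% | 0.690 | 69.4% |
| 39.8%, 30% | 10% | 30% | 15, 33 | 37.3%, 23.1% | 0.56 | 98.3% |
| 39.8%, 30% | 30% | 10% | 44, 11 | 31.6%, 27.8% | 0.86 | 19.2% |
| 39.8%, 39.8% | 10% | 30% | 15, 44 | 37.3%, 31.6% | 0.81 | 34.0% |

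**4. If event-free patients are removed too.** With a share g of them excluded, the rate is p(1−f)/[p(1−f) + (1−p)(1−g)]. For f = 30% and g = 20% in both arms:
- control: 0.2786/(0.2786 + 0.4816) = 36.6%
- drug: 0.21/(0.21 + 0.56) = 27.3%
- HR 0.698

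At g = f the rates return to 39.8% and 30%. The distortion therefore depends on recurrent patients being removed more often than event-free ones.

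**5. The two sections side by side.** Selection of populations excludes premature discontinuation and missing primary data from the PPS. Processing of missing data keeps patients who drop out half-way, as censored. Read together, they can keep an event-free patient who left early and remove a recurrent patient who stopped early, which is the imbalance that step 4 shows to matter.

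**The case against.** The SAP does not say that patients stop study drug after a recurrence. It plans a 1-year course with drug re-issued at each follow-up visit, so f may be close to zero. Adherence might be computed only while the patient is on drug, perhaps as set out in the protocol, which was not available; the example patient would then pass that rule. The duration rule speaks of a procedure, and applying it to capsules is an interpretation, though a natural one, since the capsule is what was randomised. All of this stands. It makes the fault latent and its size unknown, but the wording still permits the exclusion.

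A reader might infer that the PPS overstates the drug's benefit. The SAP does not support that. Under equal stopping the hazard ratio is almost unchanged. A false benefit needs more stopping after recurrence on drug than on placebo, and nothing in this double-blind trial points to such a difference. The reverse pattern would hide a benefit.

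A reader might also infer that the PPS can no longer inform the mITT result at all, or that the trial's main conclusion is at risk. A shift from 0.703 to 0.690 does not justify the first, and the primary analysis uses the mITT set. The PPS is the only analysis labelled a sensitivity analysis, but the Additional analysis section also re-runs the endpoints after excluding patients still on antiarrhythmic drugs beyond 90 days.

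Finally, one PPS serves every efficacy endpoint. For atrial fibrillation load, echocardiography and SF-36 at 1 year, full-course adherence is a coherent requirement, so a cut at recurrence throughout would be wrong.

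**Conclusion.** The point holds, limited to the PPS analysis of the primary endpoint. As written, the rules can delete an observed primary event because of behaviour after it, and no other section prevents this. The mITT test is untouched.

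Size and direction cannot be determined from the SAP. Equal removal mainly costs events and power and lowers both recurrence rates. Unequal removal of 10% and 30% moves the illustrative hazard ratio to between 0.56 and 0.86, depending on which arm loses more. These figures rest on assumed stopping shares, on no exclusion of event-free patients and, for the day-292 figure, on a 365-day denominator. The part on discontinuation also depends on reading procedure as study drug. The change is worth making because it is cheap and removes an avoidable source of bias.

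**What to change.** In Selection of populations:

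- For the primary recurrence analysis only, assess adherence (doses taken divided by doses due) and premature discontinuation from first dose to the earlier of first counted recurrence or the censoring date. State that stopping study drug after that date is not a major deviation for this endpoint.
- Keep full-course adherence for the PPS used for the 1-year secondary endpoints, and define its denominator.
- In the allocation and duration criterion, write study drug in place of procedure.
- Reconcile this section with Processing of missing data, so that it is clear whether a patient who drops out half-way is in the PPS as censored or excluded.

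This alters an analysis rule only and has no bearing on how patients are treated. The cost is SAP wording, an endpoint-specific PPS flag, and adherence up to recurrence that is approximate to the nearest dispensing visit.
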